### Research ethics approval and consent

This study protocol (version 1.1 dated 12 March 2025) has been approved by the Ethics Committee of the lead study site (Technical University of Munich) with the reference number 2024–630-S-NP. In addition, each participating site’s local Ethics Committee has reviewed and approved the protocol prior to initiating the study at that site or has accepted the lead site’s approval in a multi-center framework. No patients will be enrolled at a site until that site has obtained the necessary ethical approval.

All participants (or their legal representatives) provide written informed consent before any study procedures. The consent form describes the study interventions, that participants will be randomized to one of two standard treatments, and outlines potential risks/benefits. It emphasizes that participants are free to withdraw at any time. Patients are informed that their pseudonymized data will be collected, stored, and used for research, and that monitors/auditors may review their records. Consent for publication of results is included in the consent.

analyses will be applied to the secondary outcomes with pairwise between-group comparisons at 12 weeks and 6 months. The estimated mean and standard error and the 95% confidence interval (CI) for the mean treatment effect will be reported for each follow-up time point. Differences between surgical and non-operative treatments will be assessed by estimating the main effects of treatment as well as time-and-treatment interactions. For binary outcomes generalized estimating equations will be used. Treatment effects will be estimated as differences in estimated proportions. Each estimated outcome score will be plotted by treatment group to illustrate change over time. No adjustments will be made for multiple comparisons.

Sensitivity analysis of the primary endpoint will be done by repeating the primary endpoint analysis “as treated” by counting each patient who was treated surgically in the surgical group, regardless of whether they were assigned to the surgical group or crossed over at a later time point.

Adverse events will be coded with MedDRA prior to analysis.

Primary and secondary analyses will use all available data at the pre-determined time points. The extent of missing data will be calculated at each time-point. Patients with missing data at the 3-month time point will be compared to those who participated in all visits. Variables asso-ciated with missing data and baseline characteristics will be included as covariates in the mixed model as a further sensitivity analysis of the primary endpoint. Additionally, multiple im-putations will be used on data for each outcome measure at each time point. The results will be presented as adjusted mean or percentage and treatment effect including 95% CI from the 10 iterations.

No interim analysis for efficacy is planned, so the study will continue until full enrolment is reached or unless stopped early for safety or futility by recommendation of the SMB.

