### Sample size calculation

Assuming a non-inferiority study design with a one-sided α = 0.025, we set the expected difference in change of BI scores between the two groups to 0. Unnanuntana et al. (2018) show that the minimal clinically important difference (MCID) of the BI in elderly patients after a surgical intervention is 9.8 [48]. Bouwstra et al. (2018), conclude the smallest detectable change in BI in a geriatric nursing home population to be 3.0 [32]. It is common practice to choose a non-inferiority margin for a patient-reported outcome such as the BI, which is lower than the MCID, see Copay et al [49]. Thus, we set the non-inferiority margin to 5, which is closer to the smallest detectable change than to the MCID and therefore more conservative. The standard deviation of the difference in BI between baseline and week 12 was estimated at 12.7 referencing prior work by Unnanuntana et al [48]. Based on these assumptions, a sample size of 137 in each group (274 in total) will have 90% power to reject the null hypothesis of the one-sided 2.5% significance level t-test that the surgical group is inferior to the conservative group in favor of the alternative hypothesis that the surgical group is non-inferior to the conservative group. Assuming a drop-out rate of 15%, a total of 322 patients will need to be included (161 per arm).

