### Statistical analyses

Analysis will be performed on all patients who were randomized to the study. The primary estimand and its attributes are described in Table 1.

**Table 1 pone.0337999.t001:** Definition of all five attributes used to construct the primary estimand for the SCORE study (non-inferiority setting).

Primary estimand	
**Population**	Geriatric patients with recent type II & III odontoid fractures (as defined by trial inclusion/exclusion criteria).
**Variable**	Functional status accessed as the change in Barthel Index (BI) between baseline and 12 weeks thereafter
**Treatment**	• Surgical stabilization C1-2 by dorsal screw-rod construct (duration of treatment: Approximately 100 min + approximately 6 days hospital stay) or • Conservative therapy by external cervical collar immobilization (duration of treatment: 12 weeks)
**Population-summary measure**	Mean difference, including 95%CI.
**Intercurrent event (IE) and strategy**	• Refusal of therapy as randomized – multiple imputations (hypothetical estimate) • Crossover from the conservative to the surgical arm after randomization but before week 12 – use the last available BI value before surgery as best estimate of the hypothetical BI value at week 12 *Note: Cross-over from the conservative to the surgical arm after week 12 is allowed, as it does not influence the primary variable, which is measured at week 12* • Loss to follow-up after start of therapy – multiple imputations; missing at random assumed • Death – (expected ca. 10%) multiple imputations (hypothetical estimate)

Intercurrent events (IEs) will be dealt with using a hypothetical strategy to determine the treatment effect without the abovementioned IEs.

The primary endpoint will be tested using a mixed model for repeated measures (MMRM) of BI, where treatment, time, their interaction, baseline BI scores, age, and CCI will be fixed covariates, and study center will be a random covariate. In case the model does not converge due to small centers, the covariate center will be abandoned. The adjusted mean difference between groups in the primary outcome will be tested at the 12-week time point.

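### As written, the as-treated sensitivity analysis uses Barthel Index values from before the operation as surgical outcomes, and its grouping has no week-12 cut-off

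*Protocol article*

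**What the plan says.** The sensitivity paragraph belongs to the statistical analyses, although the article prints it under Research ethics approval and consent. It repeats the primary endpoint analysis and changes the grouping: every patient who was operated on counts as surgical, "regardless of whether they were assigned to the surgical group or crossed over at a later time point". It states no other change and no time limit.

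Table 1 (Statistical analyses) sets the value that a crossover patient contributes when surgery comes before week 12: "use the last available BI value before surgery as best estimate of the hypothetical BI value at week 12". The note below that rule adds: "Cross-over from the conservative to the surgical arm after week 12 is allowed, as it does not influence the primary variable".

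Two other places bear on this:
- Measures taken limits crossover surgery to the period up to week 12, and schedules Visit 2 and Visit 4 (6 months) afterwards.
- The crossover entry in the list of data to be collected also stops at week 12. It lists Visits 1, 2 and 4 after crossover, and then the patient's study ends.

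Neither place schedules a 12-week visit after crossover.

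**The concern.** The carried-forward value in Table 1 stands in for what the patient would have scored at week 12 without surgery. That has a meaning while the patient is analysed in the collar group. Once the patient is moved to the surgical group, the same number is read as an outcome of an operation that had not yet taken place, and it estimates nothing of interest.

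The missing cut-off creates the same problem by another route. A patient operated on after week 12 has a 12-week BI measured in the collar, yet the grouping rule as worded would count it as surgical.

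Crossover is the central intercurrent event in this trial, and this is the only sensitivity analysis that handles it differently from the primary analysis. The article's other sensitivity analyses concern missing data. If the as-treated result agrees with the primary one it will be read as robustness, and if it disagrees it will be read as fragility. Neither reading would be justified.

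**Working it through.** **The plan's own figure.** The design inputs are in Sample size calculation:
- Error rate: "Assuming a non-inferiority study design with a one-sided α = 0.025".
- Margin, in BI points: "we set the non-inferiority margin to 5".
- Assumed true effect: "we set the expected difference in change of BI scores between the two groups to 0".
- Spread of the outcome: "The standard deviation of the difference in BI between baseline and week 12 was estimated at 12.7".
- Resulting size and power: "a sample size of 137 in each group (274 in total) will have 90% power".

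The check runs as follows:
- Normal approximation: 2 × (1.960 + 1.282)² × 12.7² / 5² = 135.6, so 136 per arm.
- Noncentral t: 137 per arm gives power 0.901.
- Dropout: 274 / 0.85 = 322.4, stated as 322.

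The sample size reproduces and is not in dispute.

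**Which value a crossover patient contributes.**
1. The analysis is the primary one repeated, so its data rules carry over unless changed, and no change is stated.
2. For crossover before week 12, the primary rule is the last BI before surgery.
3. The post-crossover visits named in the text are surgery, discharge (at most 14 days after surgery) and 6 months. None of these is a 12-week assessment.
4. So the value is pre-operative and the label is surgical.

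**Size, with no true difference.** Let c be the share of the collar arm that crosses over. Let d be the number of points by which their pre-operative BI change lies below that of the other collar patients. The protocol gives neither. The two arms are equal in size before regrouping, so a share c/(1+c) of the as-treated surgical group carries a pre-operative value: 9.1% at c = 10% and 16.7% at c = 20%.

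*Set-up A: the deficit arises because the last BI was taken early.* The remaining collar patients and the patients randomised to surgery have the same mean m, and crossover patients are recorded at m - d.
- As-treated surgical mean: [m + c(m - d)] / (1 + c) = m - dc/(1+c)
- As-treated collar mean: m
- Difference: **-dc/(1+c)**
- Primary carry-forward difference on the same data: m - [m - cd] = +cd

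*Set-up B: the deficit arises because patients with a poorer course cross over.* The whole collar arm, with crossover patients at their pre-operative values, has the same mean m as the surgical arm. The remaining collar patients are then at m + cd and crossover patients at m + cd - d.
- As-treated surgical mean: m - cd(1-c)/(1+c)
- As-treated collar mean: m + cd
- Difference: -cd[(1-c) + (1+c)]/(1+c) = **-2dc/(1+c)**
- Primary carry-forward difference: 0

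| c | d | A: -dc/(1+c) | B: -2dc/(1+c) |
|---|---|---|---|
| any | 0 | 0 | 0 |
| 10% | 5 | -0.5 | -0.9 |
| 10% | 10 | -0.9 | -1.8 |
| 10% | 15 | -1.4 | -2.7 |
| 20% | 5 | -0.8 | -1.7 |
| 20% | 10 | -1.7 | -3.3 |
| 20% | 15 | -2.5 | -5.0 |

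**Effect on the non-inferiority conclusion.** This uses set-up A, d = 10, 137 evaluable per arm before regrouping, and SD 12.7 in both groups. The chance that the lower 95% limit lies above -5 is Φ[(5 + shift)/SE - 1.96], with SE = 12.7 × √(1/n₁ + 1/n₂).
- No crossover: SE 1.53, chance 90%.
- c = 10% (groups of about 151 and 123): SE 1.54, (5 - 0.91)/1.54 - 1.96 = 0.69, chance 76%.
- c = 20% (groups of about 164 and 110): SE 1.57, (5 - 1.67)/1.57 - 1.96 = 0.17, chance 57%.

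**The missing cut-off.** Set side by side, the Table 1 note allows crossover after week 12, Measures taken and the data list describe it only until week 12, and the as-treated rule names no limit. If the note applies, patients operated on after week 12 are regrouped with a collar-period BI. If the window applies, this part does not arise. The passages cannot all stand.

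**The case against.** The strongest reply is that the article never says expressly which BI value a crossover patient contributes once regrouped. The Table 1 rule was written for the collar label, so it may be meant to lapse here, with the missing week-12 value left to the mixed model or to multiple imputation. The article also condenses a fuller protocol, and an analysis plan may supply the rule. It is true that the carry-over is inferred. But the imputation reading is stated nowhere and sits badly with repeating the primary analysis. An analysis plan could change the rule, but it could not produce a 12-week BI that was never collected.

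On timing, a later time point may mean only later than randomisation, and two sections confine crossover to the first 12 weeks. That stands, so this part is a conflict to reconcile and not an established error.

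Loss of the protection of randomisation belongs to any as-treated analysis, and this one is openly labelled as such. That alone is no defect.

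Three stronger readings are tempting, and the document does not support them:
- *The analysis favours surgery.* If crossover patients are failing in the collar, their low scores lower the surgical mean and leave the collar mean. The shift is then against surgery, and non-inferiority becomes harder to show.
- *It is the only sensitivity analysis of the primary endpoint.* The article adds one with covariates associated with missing data, and also multiple imputation.
- *The artefact is certain or large.* No crossover rate is planned. The 50-60% in the Discussion is collar failure from non-compliance without nursing support, not a crossover rate. Crossover may also follow a patient's request, so a deficit is plausible but not given.

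**Conclusion.** The point holds for the as-treated analysis as written: pre-operative collar scores are analysed as surgical outcomes, and the grouping lacks a week-12 limit that the rest of the text does not supply consistently.

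With no true difference, the artefact for 10-20% crossover and a 10-point deficit is -0.9 to -1.7 BI points if the remaining collar patients match the surgical arm. It is -1.8 to -3.3 if the collar arm as a whole does. It reaches the margin of 5 only at the pessimistic end (20%, 15 points, second set-up), and it is 0 without a deficit. Crossover share, deficit and set-up are all assumptions.

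In the first set-up the same carried-forward values move the primary estimate by +1.0 to +2.0 and the sensitivity estimate by -0.9 to -1.7. A disagreement between the two would then say nothing about the treatments.

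The defect is confined to a sensitivity analysis. It should be fixed, but it does not by itself undermine the primary analysis or the sample size.

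**What to change.** 1. In the as-treated analysis, count as surgical only patients operated on before their 12-week assessment. Do not use a pre-operative BI as their surgical outcome. Label the analysis exploratory.
2. Reconcile the Table 1 note with the crossover window in Measures taken and in the list of data to be collected.
3. Collect BI at 12 weeks from every patient regardless of crossover. Use it in an as-randomised (treatment-policy) analysis, named as the sensitivity analysis for crossover.

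The cost is a wording change in the protocol and analysis plan, one extra BI contact for crossover patients and a little more analysis work. Item 3 should be settled early, because 12-week scores that are not collected cannot be recovered.

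### Ten imputations is a low number: if the non-inferiority verdict is read from imputed data, it changes with the seed in about 3% of trials at the planned 15% missing

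*Protocol article*

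**What the plan says.** Table 1 (Statistical analyses) handles three of the four intercurrent events of the primary estimand by multiple imputation. For loss to follow-up the entry is "multiple imputations; missing at random assumed". For death it is "expected ca. 10%) multiple imputations (hypothetical estimate". Refusal of the randomised therapy is also imputed, with no rate given. The fourth event, crossover before week 12, takes the last Barthel Index (BI) before surgery and is not imputed.

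Below Table 1, the primary endpoint is tested with a mixed model for repeated measures (MMRM) at 12 weeks. The statistical text that runs on under the heading Research ethics approval and consent says that primary and secondary analyses use all available data. It then adds multiple imputation for every outcome at every time point, reporting the "treatment effect including 95% CI from the 10 iterations". This is the only number of imputations that the article gives.

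The design figures are in Sample size calculation. The test is one-sided at 0.025. On the true difference, the text reads "we set the expected difference in change of BI scores between the two groups to 0". On the margin, it reads "we set the non-inferiority margin to 5". On variability, it reads "The standard deviation of the difference in BI between baseline and week 12 was estimated at 12.7". Drop-out is set at 15%, which gives 161 per arm.

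**The concern.** A multiple-imputation estimate carries Monte Carlo error that shrinks only as the number of data sets grows. That error is small beside the width of the confidence interval. The confirmatory question here, however, is a yes/no reading of one confidence limit against -5, so what matters is how often the reading changes when the same data are imputed again. If that is not rare, two analysts who follow the same plan could report opposite conclusions from the same trial. Few imputations also widen the pooled interval slightly, which costs power.

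**Working it through.** **Inputs.** From Sample size calculation: margin 5, SD 12.7, true difference 0, one-sided 0.025, 161 per arm randomised, 15% drop-out. From Table 1: deaths about 10%. Assumption: the fraction of missing information, λ, equals the share of patients imputed, with no help from auxiliary data. *Iterations* is read as imputed data sets.

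**The plan's own figure.** The plan states "a sample size of 137 in each group (274 in total) will have 90% power". The exact noncentral t calculation gives power 0.8988 with 136 per arm and 0.9009 with 137, so 137 is reproduced. Then 274/0.85 = 322.4, which agrees with the stated 322 apart from rounding.

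**Variances.** Let U be the complete-data variance of the difference, T the total variance with unlimited imputations, B the between-imputation variance and m the number of data sets.

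- U = 2 × 12.7²/161 = 322.58/161 = 2.004
- T = U/(1 − λ) and B = λT
- Monte Carlo SD of the pooled estimate = √(B/m)

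| λ | T | B | Monte Carlo SD, m = 10 | Monte Carlo SD, m = 100 |
|---|---|---|---|---|
| 15% | 2.357 | 0.354 | 0.19 | 0.06 |
| 25% | 2.671 | 0.668 | 0.26 | 0.08 |
| 30% | 2.862 | 0.859 | 0.29 | 0.09 |

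**Hand check at 15%.** √T = 1.535 and the t quantile is about 1.969. Non-inferiority therefore needs an estimate above −5 + 1.969 × 1.535 = −1.977. Power with unlimited imputations is Φ(1.977/1.535) = Φ(1.288) = 90.1%. The density of the estimate at that threshold is 0.174/1.535 = 0.113 per BI point. The mean absolute gap between two runs is √(2 × 0.354/10) × √(2/π) = 0.266 × 0.798 = 0.212. The product is 2.4%, from noise in the point estimate alone. Variation in the pooled standard error and degrees of freedom adds the rest.

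**Simulation.** Rubin's rules: pooled variance = U + (1 + 1/m)b, where b is the between-imputation variance observed in the run, with Barnard-Rubin degrees of freedom. The verdict is positive if the lower 95% limit exceeds −5. There were 400,000 trials per cell and two independent seeds per trial.

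| λ | Two seeds disagree, m = 10 | m = 50 | m = 100 | Power, m = 10 | Power, unlimited m | Loss at m = 10 (points) |
|---|---|---|---|---|---|---|
| 15% | 3.0% | 1.2% | 0.9% | 89.5% | 90.1% | 0.6 |
| 25% | 5.5% | 2.2% | 1.5–1.6% | 84.8% | 86.3% | 1.4 |
| 30% | 7.1% | 2.8% | 1.9% | 81.7% | 83.7% | 2.0 |

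Losses are taken before rounding. A separate check that imputed simulated patient data directly gave 3.2%, 5.7% and 7.3% disagreement at m = 10. At a true difference of −5 the rejection rate with m = 10 is about 2.4% to 2.5%, so type I error is not inflated.

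**Which λ the protocol supports.** The 15% row is the stated drop-out. The 25% row applies only if the 10% deaths are additional to that 15%, which the article leaves open. The 30% row has no stated basis; it is shown as an upper scenario.

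**The case against.** The strongest counter-argument is that the primary endpoint is tested by an MMRM, that the analyses use all available data, and that imputation is introduced as an addition, just after a sensitivity analysis. On that reading the confirmatory verdict is likelihood-based and has no seed, and the 10 governs a supplementary analysis. Nothing in the article ties the 10 explicitly to the Table 1 strategies. This stands as a condition on the finding. It does not remove it, because Table 1 defines the primary estimand through imputation.

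Four stronger inferences are tempting, and the documents do not support them:

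- **That the plan's expected range reaches 7% disagreement and 2 points of power.** This needs about 30% missing information, for instance through refusals, for which no rate is given. Crossovers use a carried-forward value and add no imputation noise, and a 6-month BI used in the imputation model would lower λ.
- **That 10 imputations make the test invalid.** Type I error stays at its nominal level.
- **That the article is deficient because it names no seed.** The seed is routine content of an analysis plan that is not shown here. Fixing it would make a run repeatable, but the verdict would still rest on an arbitrary choice.
- **That the two-seed figure is the rate of wrong verdicts.** It is the larger of two measures. Against the verdict with unlimited imputations, m = 10 differs in 2.1% of trials at λ = 15%.

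It is also true that more imputations reduce disagreement without abolishing it, and that 0.6 points of power is small.

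**Conclusion.** The point holds, conditionally, as a minor improvement. If the non-inferiority conclusion comes from the imputed data, 10 data sets leave it dependent on the seed in about 3% of trials at the planned 15% missing, with about 0.6 points of power lost. The figures are about 5.5% and 1.4 points if deaths are additional to the drop-out allowance. If the conclusion comes from the MMRM on observed data, only the added analysis is affected.

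The figures assume SD 12.7, 161 per arm, λ equal to the share imputed and a true difference of 0. At λ = 15% and m = 10, disagreement would be 6.6% at a true difference of −2 and 0.9% at −5. The unclear relation between the MMRM and the imputation matters more than the number 10 and should be settled at the same time.

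**What to change.** Replace 10 by 100 imputed data sets (at least 50) wherever multiple imputation is used, for primary and secondary outcomes, and call them imputed data sets instead of iterations. With 100, two-seed disagreement falls to about 0.9% at 15% missing and about 1.6% at 25%, and the power loss to 0.2 points or less across 15% to 30%.

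Add one sentence stating whether the confirmatory result comes from the MMRM on observed data or from the imputed data, so that Table 1 and the analysis text agree.

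The cost is one number, one sentence and minutes of computing. Sample size, visits and data collection do not change.
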